### **1.7 Sampling**

#### **1.7.1 Study Population**

The study population recruit for this study will be among the MMT clients registered with the government health clinics facilities from all districts in Malacca.

#### **1.7.2 Sample Population**

The sample population will be all registered MMT clients in government health clinics in Malacca attending the MMT clinic from October 2022 until May 2023.

#### **1.7.3 Selection Criteria**

##### **1.7.3.1 Inclusion Criteria**

The inclusion criteria are:

- i. Age 18 years and above
- ii. Active MMT clients of government health clinics in Malacca

- iii. Negative hepatitis C status or positive hepatitis C status but not on treatment.

#### 1.7.3.2 Exclusion Criteria

The exclusion criteria are:

- i. MMT clients diagnosed with hepatitis C and ever or currently on treatment regardless of the sustained virologic response (SVR) status.
- ii. MMT clients currently involve in any intervention studies or involved in any intervention study completed within one year before initiation of this study.

#### 1.7.4 Sampling Frame

The list of registration number of MMT clients from the methadone registry obtained from Malacca State Health Department.

#### 1.7.5 Sampling Unit

The sampling unit will be individual who is active MMT clients of government health clinics in Malacca.

#### Sampling Method

The list of MMT clients based on the registration number were screen for eligibility criteria. Those who does not fulfil the eligibility criteria will be remove from the list. Subsequently, the cleaned registration number list will be arranged in ascending order. Following that each client will be assigned number starting from number one to total number of the population. In the next step simple random sampling will be conducted using online random number generator from <https://stattrek.com/statistics/random-number-generator.aspx> website to recruit participant according to number of sample size required.

#### 1.7.6 Sample Size Estimation

The sample size calculation for this study was calculated based on the primary outcome desire which is willingness for hepatitis C treatment. The sample size calculation will be calculated using the formula for testing the different in proportion between two groups (Lwanga et al., 1991). The formula and calculation are as depicted below:

$$n = \frac{\{[Z_{(1-\alpha/2)} * \sqrt{2\bar{P}(1-\bar{P})}] + [Z_{(1-\beta)} * \sqrt{P_1(1-P_1) + P_2(1-P_2)}]\}^2}{(P_1-P_2)^2}$$

$$n = \frac{\{[1.96 * \sqrt{1.19(1-0.405)}] + [0.842 * \sqrt{0.1875 + 0.2464}]\}^2}{(0.31)^2}$$

$$n = 39$$

Thus, the sample size calculated is equal to 39 for one arm. Total sample size for both control and intervention groups are 78 persons (39 x 2). Following that, an additional adjustment for dropouts were made based on the 77% attrition rate from previous study (Arain et al., 2016). Therefore, the adjustment for response rate is 78/(1-L) (L= attrition rate) = 78/0.33= 236 (118 respondents per arm) (KK Gupta et al., 2016). Thus, the sample size needed for this study is 118 pairs of intervention and control groups which amount to 236 subjects. The information used for sample size calculation is as

presented in Table 3.1. The calculation was based on findings from a randomize control trial study for willingness of hepatitis C treatment (Arain et al., 2016).

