**Table 3.1. Information for sample size calculation**

| Study Characteristic | Assumption made by investigator                                                                                                                        |
|----------------------|--------------------------------------------------------------------------------------------------------------------------------------------------------|
| Type of study        | Randomize Control Trial                                                                                                                                |
| $Z_{(1-\alpha/2)}$   | $Z_{(1-\alpha/2)} = 1.96$ , the value of the standard normal distribution corresponding to a significance level of alpha of 0.05 for a two-sided test. |
| $Z_{(1-\beta)}$      | $Z_{(1-\beta)} = 0.842$ , the value of the standard normal distribution corresponding to the desired level of power of 80%.                            |
| $P_1$                | $P_1 = 0.75$ , Proportion of respondent willing for treatment in intervention group at 3 months post intervention                                      |
| $P_2$                | $P_2 = 0.44$ , Proportion of respondent willing for treatment in control group at 3 months post intervention                                           |
| $\bar{P}$            | $\bar{P} = (0.75 + 0.44) / 2$ , $\bar{P} = 0.595$                                                                                                      |

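### The dropout inflation in section 1.7.6 contradicts itself: 77% attrition requires a divisor of 0.23 (total 340), but the protocol divides by 0.33 to reach 236; if 77% is right, 236 gives about 65% power, not 80%

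*Protocol*

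**What the plan says.** Section 1.7.6 (Sample Size Estimation) sizes the trial on the primary outcome, willingness for hepatitis C treatment, with a formula for two proportions. It reaches 39 per arm and then: "Total sample size for both control and intervention groups are 78 persons (39 x 2").

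It next allows for loss to follow-up: "an additional adjustment for dropouts were made based on the 77% attrition rate from previous study". The step is written as "Therefore, the adjustment for response rate is 78/(1-L) (L= attrition rate) = 78/0.33= 236 (118 respondents per arm"). The section ends with 236 as the number needed.

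Table 3.1 gives the inputs:
- Z = 1.96, "corresponding to a significance level of alpha of 0.05 for a two-sided test".
- Z = 0.842, "the value of the standard normal distribution corresponding to the desired level of power of 80" per cent.
- P1 = 0.75, "Proportion of respondent willing for treatment in intervention group at 3 months post intervention".
- P2 = 0.44, "Proportion of respondent willing for treatment in control group at 3 months post intervention".

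No other part of the protocol gives a different attrition rate.

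**The concern.** The protocol defines L as the attrition rate, sets it at 77%, and then puts 0.33 where 1-L belongs. One minus 0.77 is 0.23. The recruitment target therefore does not follow from the stated rate and the stated formula.

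This matters because 236 is the number to be drawn from the methadone registry, and the 80% power claim for the primary outcome depends on about 78 participants remaining at three months. If the stated loss is the true expectation, the target falls well short of that. If it is not, the protocol misreports the assumption behind its sample size. In both cases a reader cannot tell from the text what loss the trial was built to withstand.

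**Working it through.** **Inputs.** P1 = 0.75, P2 = 0.44, mean 0.595, two-sided alpha 0.05 (1.96), power 80% (0.842), all from Table 3.1. The 39 per arm, the 77% attrition, the formula 78/(1-L), the divisor 0.33 and the total 236 are from section 1.7.6.

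**1. Base sample size.**

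n = {1.96 × √(1.19 × 0.405) + 0.842 × √(0.1875 + 0.2464)}² / 0.31²
= (1.3607 + 0.5546)² / 0.0961 = 38.2, rounded up to 39 per arm, 78 in total.

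The stated 39 reproduces, so the fault lies only in the inflation step.

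**2. Inflation step.**

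| Reading of the rate | Divisor | Total needed |
|---|---|---|
| 77% attrition, as stated | 0.23 | 78/0.23 = 339.1, so 340 |
| 67% attrition, implied by the divisor used | 0.33 | 78/0.33 = 236.4 (protocol: 236) |
| 77% retention (assumption; not supported by the protocol) | 0.77 | 78/0.77 = 101.3, so 102 |

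The other common way of inflating, 78 × 1.77 = 138, does not give 236 either. Only 0.33 does. Against 340, the stated target is 340 - 236 = 104 short.

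**3. Power of 236 under each reading.** Solving the protocol's formula for power with m completers per arm:

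z = {0.31 × √m - 1.96 × √(1.19 × 0.405)} / √(0.1875 + 0.2464), power = Φ(z)

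| Loss | Completers in total | m per arm | z | Power |
|---|---|---|---|---|
| 77% | 236 × 0.23 = 54.3 | 27.1 | (1.6150 - 1.3607)/0.6587 = 0.386 | 65.0% |
| 67% | 236 × 0.33 = 77.9 | 38.9 | (1.9345 - 1.3607)/0.6587 = 0.871 | 80.8% |
| 23% (if 77% is retention) | 236 × 0.77 = 181.7 | 90.9 | (2.9549 - 1.3607)/0.6587 = 2.420 | 99.2% |

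Exact enumeration of the uncorrected chi-square test at 27 per arm gives 64.0%, so the normal approximation is not the cause of the shortfall.

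**4. Detectable difference.** With a 44% control rate and 80% power, the same formula gives about 31 points at 39 per arm and about 36 points at 27 per arm.

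**5. A separate clerical slip.** The printed substitution shows (1-0.405) where (1-0.595) is meant. Taken literally it would give 50.5, so 51 per arm. The stated 39 comes from the correct value, so the slip has no bearing on the steps above.

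**The case against.** The strongest reply is that the percentage, not the divisor, is the misprint. The 0.33, the 236 and the 118 per arm agree with each other and with the stated 80% power, while 77% is printed once and stands alone. Changing one digit, to 67%, would make the paragraph correct with no change to the target. This stands: the documents do not settle which figure is wrong.

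For that reason a reader might infer that the trial is shown to have only 65% power, and the documents do not support that. By the same formula 236 keeps 80% power up to about 67% loss, so the shortfall exists only if 77% is the real expectation.

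A second reply is that 65% is not the power of the planned analysis. Section 1.15.1 plans a generalized linear mixed model over three time points, and section 1.15.2 adopts intention to treat. That is also fair. The figure is a check on the protocol's own premise, a two-proportion comparison in completers, and should be described that way.

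In the other direction, a reader might argue that power is lower still because section 1.6 calls the trial cluster randomized and no design effect is applied. But section 1.8 describes allocating individual respondents, and no intracluster correlation is given, so no further loss can be quantified here.

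None of these replies makes 77%, 0.33 and 236 compatible.

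**Conclusion.** Wrong as written. On the protocol's own definition, 77% attrition leads to 340 participants, not 236. That part rests on simple arithmetic and is certain.

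The effect on power is conditional. If 77% is right, about 54 completers remain and power is about 65% for 75% versus 44%. If 67% was meant, about 78 remain, power is about 81%, and the error is confined to the printed percentage. These figures assume equal loss in the two arms, analysis of completers only, individual allocation, and the proportions in Table 3.1. The retention reading (102 needed, about 99% power with 236) is included only for completeness, because nothing in the protocol supports it and the cited study is not available here.

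**What to change.** Check the attrition figure in the cited study, then make L, the divisor, the total and the stated power agree:

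- **If 77% attrition is right:** state that the formula gives 340. If 236 is kept, state about 54 completers, about 65% power by the protocol's formula, and a detectable difference of about 36 points from a 44% control rate. Enrolling more or accepting the lower power is the sponsor's choice.
- **If 67% is right:** correct 77% to 67% and keep 236.
- **If the 77% turns out to be retention:** write L = 0.23 and a required total of 102, and state that 236 gives about 99% power.

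In the same edit, change the printed (1-0.405) to (1-0.595).

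The cost is a few lines of protocol text. Extra recruitment, 104 participants, arises only if 77% is confirmed and the sponsor chooses to preserve 80% power. If 77% is confirmed and 236 is kept, the only cost is a less favourable stated power.

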**Table 3.1. Information for sample size calculation**

| Study Characteristic | Assumption made by investigator                                                                                                                        |
|----------------------|--------------------------------------------------------------------------------------------------------------------------------------------------------|
| Type of study        | Randomize Control Trial                                                                                                                                |
| $Z_{(1-\alpha/2)}$   | $Z_{(1-\alpha/2)} = 1.96$ , the value of the standard normal distribution corresponding to a significance level of alpha of 0.05 for a two-sided test. |
| $Z_{(1-\beta)}$      | $Z_{(1-\beta)} = 0.842$ , the value of the standard normal distribution corresponding to the desired level of power of 80%.                            |
| $P_1$                | $P_1 = 0.75$ , Proportion of respondent willing for treatment in intervention group at 3 months post intervention                                      |
| $P_2$                | $P_2 = 0.44$ , Proportion of respondent willing for treatment in control group at 3 months post intervention                                           |
| $\bar{P}$            | $\bar{P} = (0.75 + 0.44) / 2$ , $\bar{P} = 0.595$                                                                                                      |

## 1.8 Randomisation

### 1.8.1 Sequence Generation

Upon recruiting the participant who fulfil the eligibility criteria according to sample size calculated, random allocation sequence will be generated to allocate respondents into either intervention or control groups. Randomization sequence will be generated using software from web page “Create a block randomization list” (Sealed Envelope Ltd, 2019) .

In this study, the permuted block randomization will be used to allocate respondent into either the intervention or control group. This permuted block randomization will be conducted using the software from web page “Create a block randomization list” (Sealed Envelope Ltd, 2019). The flow chart of study design will be presented by adopting the CONSORT 2010 flow diagram in the result section after conducting the study as presented in Figure 3.2 (Moher et al., 2010).

[figure not shown]

**Figure 3.2. Flow Chart of Study Design and Outcome Evaluation**

### 1.8.2 Allocation Concealment

In this study, the allocation concealment method that will be use is the “sequentially numbered, opaque, sealed enveloped methods” as depicted in Figure 3.3. In the process of randomization and allocation concealment, a randomization list will be generated using software from web page “Create a block randomization list” (Sealed Envelope Ltd, 2019). The list will also include unique allocation codes generated by the software which consist of two letters followed by 1 or more digits (E.g: BW2, AM4, AB1 and etc). This unique code will represent either the intervention or the control group and meaning of the code will only be known by the sequence generator. This will ensure concealment of the allocation. Following that, the “sequentially numbered, opaque, sealed enveloped methods” will be use during respondent recruitment. The unique code will be print out, cut out and sealed in opaque envelops. Subsequently, as patient were being recruited, the opaque enveloped containing the different code will be pulled out by liaison officer at each clinic. The randomisation code will only be release after patient have been recruited into the study which take place after the baseline measurement have been completed. By doing this, the parties involve during the randomization process will be blind from the group that the respondent will be allocate

[figure not shown]

**Figure 3.3. Allocation concealment process**

### 1.9 Blinding

This study will use the single blinding method in which the respondent will not be aware of their group status.

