### **1.6 Study Design**

This study is a two-armed, parallel, single blinded, cluster randomized controlled trial (CRCT).

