#### 1.10.1 Development of Health Intervention Module

The health intervention module will be developed in Malay language and validated by the supervisory committee and other expert from Universiti Putra Malaysia (UPM) and Malacca State Health Department. The expert will consist of Public Health specialist and Family Medicine Specialist. Figure 3.4 summarize the flow of health education module development.

[figure not shown]

**Figure 3.4. The schematic diagram for the development of the health education module on increasing willingness for hepatitis C treatment**

The intervention will be delivered during MMT client's appointment with the medical officer in charge of the MMT programs in the form of brief intervention module. The medical officer involve with the study will be brief and undergo training on proper way to conduct questionnaire interview and deliver health education intervention module to the clients. Prior to the intervention session, a baseline assessment will be conducted using validated questionnaire to measure their knowledge regarding hepatitis C, attitude towards hepatitis C infection, subjective norm on hepatitis C treatment, perceived behavioural control on hepatitis C treatment and willingness for hepatitis C treatment. Following that, the brief intervention will be deliver face to face by the medical officer in charge using several materials provided by researcher. The estimated duration of the intervention session is around one and half hours. Table 3.2 summarized the application of TPB constructs in the development of the health education intervention module.

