### 1.10.2 Questionnaire

Questionnaire that will be use is a self-administered questionnaire that will be distributed to respondent in Malay language. Estimated duration to answer the questionnaire is 20 minutes. The questionnaire section related to knowledge of hepatitis C and construct of TPB will be adopted from previous study. The validity and reliability assessment of the questionnaire will be discussed in respective sections. The set of questionnaires for this study will contain

- i. Section A for Sociodemographic characteristics  
This section will ask regarding respondent sociodemographic characteristics which include age, gender, race, marital status, employment status, monthly income, and education level.
- ii. Section B for MMT treatment profile  
This section will explore regarding history of MMT treatment which include current Methadone dose in mg/day and duration of MMT treatment in years.
- iii. Section C for HIV and Hepatitis C status  
This section will explore regarding respondents HIV and hepatitis C screening history and current HIV and hepatitis C status.
- iv. Section D for history of hepatitis C educational program  
This section will explore regarding respondents' history of attending any hepatitis C educational program.
- v. Section E for substance use history  
This section will explore regarding history of smoking and history of ever and past 6 month injecting and non-injecting drug use as well as alcohol use history among the respondents.
- vi. Section F for willingness for hepatitis C treatment  
This section will explore regarding respondent willingness for hepatitis C treatment is they were diagnosed with hepatitis C and offered for treatment. Respondent will need to select between yes or no to indicate their willingness for hepatitis C treatment.
- vii. Section G for knowledge of hepatitis C  
This section will explore regarding respondent knowledge on hepatitis C infection, transmission, prevention, and treatment. The questionnaire in this section will be adopted from previous study by Arain et al., (2016). Total item in this scale are 19 items. The answer options will be "True", "False" and "Not sure". Each answer will be given 1 mark for "yes" answer and 0 for "no" and "don't know" answer. Total score will range from 0 to 19 and the higher the score reflect higher knowledge of respondent on hepatitis C infection.
- viii. Section H for attitude towards hepatitis C infection and treatment  

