#### **1.11.2.4 Training of the Enumerators**

Training of the enumerators will be conducted prior to commencement of the intervention. A medical officer in charged for Methadone program from each selected clinics will be appointed as the liaison officer in charge of data collection and distribution of the intervention packages (health talk and video). They will also be responsible for consent form distribution and collection. They will be train on how to conduct the health talk and response to enquiry regarding content of the intervention module.

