### **1.12 Implementation of the Health Education Intervention**

An intervention module based on the Theory of Planned Behaviour (TPB) will be delivered to the intervention group through a 20 to 30 minute face-to-face session during routine MMT clinic appointments. Conducted by trained medical officers, the intervention will take place over four months and involve randomly selected MMT clients from government clinics in Malacca.

The session includes three parts: a health talk to improve knowledge and attitudes about hepatitis C; a pre-recorded video of a patient who completed DAA treatment, aimed at enhancing subjective norms; and another video addressing common barriers to treatment.

Before implementation, medical staff will undergo training on delivering the module and conducting interviews. Participants will complete a baseline survey, followed by assessments immediately after the intervention and three months later. The control group will receive the same intervention after the final data collection.

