### Section J: Willingness for hepatitis C treatment

Based on the statements below, **circle** your answer of choice in the space provided

| Question                                                                                                                                                                       | Answer |    |
|--------------------------------------------------------------------------------------------------------------------------------------------------------------------------------|--------|----|
| Suppose you were diagnosed to have hepatitis C and was advised for hepatitis C treatment by the medical officer, are you willing to received hepatitis C treatment as advised? | Yes    | No |

THE END

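### The single-blind label does not hold for respondents in the intervention arm, and the protocol contradicts itself on how the primary yes/no answer is collected

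*Protocol*

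**What the plan says.** **Blinding.** Section 1.9: "This study will use the single blinding method in which the respondent will not be aware of their group status." Section 1.6 also labels the trial single blinded.

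**What each arm receives.** Section 1.10.1 says that "the brief intervention will be deliver face to face by the medical officer in charge using several materials provided by researcher". Sections 1.12 and 1.13 describe a health talk with recorded video. For the other arm, 1.12 says: "The control group will receive the same intervention after the final data collection." Section 1.13 lists only questionnaires for controls at baseline, T1 and T2. Section 1.14.2 makes the later session conditional on the module proving effective. No sham or attention session is described.

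**Mode of collection.** Section 1.10.2: "Questionnaire that will be use is a self-administered questionnaire that will be distributed to respondent in Malay language." Appendix A asks respondents to tick or circle their answers. But 1.10.1 trains the medical officer in the "proper way to conduct questionnaire interview and deliver health education intervention module to the clients", 1.12 again pairs module delivery with interviewing, and 1.16.2 has a site interviewer hold the completed forms.

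**Roles.** Under 1.11.2.4, the methadone medical officer at each clinic "will be appointed as the liaison officer in charge of data collection and distribution of the intervention packages". The same officer hands out and collects consent forms and is trained to give the talk. In 1.8.2 the liaison officer draws the allocation envelopes.

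**Primary item.** Appendix A, Section J is one yes/no question. It supposes a diagnosis and advice from the medical officer, then asks "are you willing to received hepatitis C treatment as advised".

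**The concern.** The primary outcome is a single subjective answer about accepting a doctor's advice. Its protection against reporting bias depends on who knows the allocation and who receives the answer. The protocol claims one safeguard, respondent blinding, that the design does not provide. It leaves a second, private self-completion, unsettled because sites could follow either instruction.

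In the intervention arm, T1 comes immediately after a session meant to produce a *yes*, and the officer responsible for the package is also responsible for the data. Controls answer the same item with no session before it. Any wish to please the officer would then tend to act more strongly in one arm and in the direction of benefit. A report that repeats the single-blind label would tell readers this risk had been controlled.

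**Working it through.** **1. Does respondent blinding hold?** No arithmetic applies; the sections are set side by side.

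| Point | What the protocol describes | Consequence |
|---|---|---|
| Intervention arm | In-person talk and video (1.10.1, 1.12, 1.13) | The respondent knows the session took place |
| Control arm | Three questionnaires, no session before T2 (1.12, 1.13) | Awareness depends on what consent disclosed; not shown |
| Sealed coded envelopes | Opened after baseline (1.8.2) | Conceal allocation beforehand; blind no one afterwards |
| Delivering officer | Gives the session (1.10.1) | Necessarily knows who received it |

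The statement in 1.9 covers respondents as a whole, so its failure in one arm is enough to make it wrong.

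**2. Is the mode of collection fixed?** Self-administered: 1.10.2 and the Appendix A format. Interview wording: 1.10.1, 1.12 and 1.16.2. These cannot all describe one procedure, and no section says which governs.

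**3. Is there an independent collector?** None is described. Section 1.11.2.4 gives data collection and the intervention packages to the same officer.

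**4. Illustrative size.** Inputs from Table 3.1: P1 = 0.75 and P2 = 0.44 at three months, a difference of 0.31. These are the values behind the plan's 39 per arm: [1.96 × √(1.19 × 0.405) + 0.842 × √(0.1875 + 0.2464)]² / 0.31² = 38.17, rounded up to 39. (The displayed line has 1 − 0.405 where 0.405 is needed; 39 follows from 0.405.)

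The protocol gives no rate of answering to please. Assume that a fraction f = 10–20% of respondents who remain unwilling in the intervention arm say *yes*, with no such shift among controls. Then shift = f × (proportion unwilling in the intervention arm).

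| Scenario | Unwilling | f = 10% | f = 20% |
|---|---|---|---|
| Planned 0.75 reached | 1 − 0.75 = 0.25 | 0.025 | 0.050 |
| No true effect | 1 − 0.44 = 0.56 | 0.056 | 0.112 |

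In the first scenario the shift is 0.025/0.31 = 8% to 0.050/0.31 = 16% of the planned difference.

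**5. What such a shift could do to the test when there is no true effect.** Let d be the shift, p2 = 0.44, p1 = 0.44 + d and p̄ their mean. Let c = 1.96 × √(2p̄(1 − p̄)/n) and s = √([p1(1 − p1) + p2(1 − p2)]/n). The chance of a significant result is Φ((d − c)/s) + Φ((−d − c)/s).

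For d = 0.10 and n = 118: c = 0.1276, s = 0.0648, and the chance is Φ(−0.43) = 34%, the second term being negligible.

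| Assumed shift | 39 analysed per arm | 118 analysed per arm |
|---|---|---|
| 0 | 5% | 5% |
| 5 points | 7% | 12% |
| 10 points | 14% | 34% |

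The 118 column assumes that everyone recruited is analysed; the protocol plans for heavy attrition, so it is an upper case.

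**The case against.** **Respondents cannot be blinded in an education trial, so this is no fault.** The first half is right, and lack of blinding alone would not be a criticism. The fault is claiming it, and leaving open a collection route that could have been closed.

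**A reader might infer that no respondent in either arm can be blinded.** The documents do not support that for controls. If consent did not disclose two arms or a deferred session, controls could remain unaware, and the consent pages are not available.

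**A reader might infer that the primary answer is taken by interview by the officer who has just delivered the session.** That is possible but not established. The only explicit statement of mode is self-administration, and the primary item is formatted for circling. Section 1.16.2 sets answering in a separate place with code numbers, no names and a confidential envelope. Interviewing may be loose wording in the training text, and the site interviewer is not identified as the delivering officer. These safeguards carry weight. They do not say, however, that the officer is out of sight or that the respondent seals the form.

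**The pressure is partly shared.** The same officer role collects data in both arms and the item is identical, so some desirability cancels in the comparison. The part tied to the session does not, because only one arm has it.

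**The planning proportions are three-month values.** At T2 no session has just ended, so the effect should be weaker there than at T1. Awareness of having had the session and the officer's dual role persist.

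**Conclusion.** The concern holds in this form. The single-blind statement in 1.6 and 1.9 is wrong for the intervention arm and unverified for controls. The mode of collecting the primary item is contradictory. One officer role spans consent, data collection and the intervention packages. Together these leave room for differential social-desirability bias in favour of the intervention, greatest at T1.

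The size of that bias is unknown. On the assumed 10–20% rate, confined to the intervention arm, it is 2.5–5.0 points if 0.75 is reached and 5.6–11.2 points if there is no true effect. A reader might go on to say that the bias amounts to 18–36% of the planned 31-point difference. That divides the no-effect shift by an effect assumed to be real; with the planned effect present the share is 8–16%.

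A reader might also conclude that the analyst must be masked. The protocol makes no claim about the analyst. Section 1.16.3 restricts data access to the principal investigator and no separate analyst is described, so masking would be an addition and is not part of this correction.

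**What to change.** - **Sections 1.6 and 1.9:** replace the single-blind label with a statement that the trial is open-label for respondents and for the officers who deliver the module.
- **Sections 1.10.1, 1.12 and 1.16.2:** remove the interview wording so that they agree with 1.10.2 and Appendix A.
- **Section 1.10.2:** state that the questionnaire is self-completed at all three visits in both arms, out of the officer's sight, and sealed by the respondent in the confidential envelope before it is handed back. Any reading help given should be recorded.
- **If collection is already complete** (1.13 is written in the past tense): correct the blinding label, report how questionnaires were actually administered in each arm, and state the resulting limit on the conclusion.

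The cost is protocol wording and one training instruction. Section 1.16.2 already provides the envelope and the separate place, and no extra participants or visits are needed. The downside is that some respondents with low literacy may need reading help, which weakens privacy for them; recording it makes that visible.
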